# (Cost-)effectiveness of an internet-based physical activity support program (with and without physiotherapy counselling) on physical activity levels of breast and prostate cancer survivors: design of the PABLO trial

**DOI:** 10.1186/s12885-018-4927-z

**Published:** 2018-11-06

**Keywords:** Physical activity, Internet-based intervention, Breast cancer survivors, Prostate cancer survivors, RCT

## Abstract

**Background:**

Higher levels of physical activity (PA) after treatment are associated with beneficial effects on physical and psychosocial functioning of cancer survivors. However, survivors often do not meet the recommended levels of PA. In order to promote PA, we developed a closed internet-based program. The aim of the study is to evaluate the (cost-)effectiveness of an internet-based PA-promotion program, alone or combined with physiotherapy counselling, compared to usual care, on PA-levels of breast or prostate cancer survivors. In this multicenter randomised controlled trial (RCT), breast or prostate cancer survivors who completed their primary treatment 3–12 months earlier, will be randomised to either 6-months access to a fully-automated internet-based intervention alone, an internet-based intervention plus remote support by a physiotherapist, or a control group. The intervention is based on the Transtheoretical Model and includes personalized feedback, information, video’s and assignments. Additionally, in a second arm, physiotherapy counselling is provided through monthly scheduled and on-demand telephone calls. The control group will receive usual care and a leaflet with PA guidelines.

**Methods:**

At baseline, 6 and 12 months, the primary outcome (PA) will be measured during 7 consecutive days by accelerometers. Secondary outcomes are self-reported PA, fatigue, mood, health-related quality of life, and costs. The group differences for primary and secondary outcomes will be analyzed using linear mixed models.

**Discussion:**

If proven to be (cost)effective, this internet-based intervention, either alone or in combination with telephone support, will be a welcome addition to previous RCT’s.

**Trial registration:**

Netherlands trial register (NTR6911), Date of trial registration: December 21, 2017.

**Electronic supplementary material:**

The online version of this article (10.1186/s12885-018-4927-z) contains supplementary material, which is available to authorized users.

## Background

Due to improved diagnostics and treatment of cancer, the number of survivors is increasing. In 2008, 28.8 million people worldwide had survived cancer at least 5 years [1]. Breast and prostate cancer have the highest prevalence of all cancers among women and men, respectively, with an incidence of 364.400 and 359.900 in the European Union in 2012 [2]. After treatment, many survivors experience negative consequences such as pain, impaired physical functioning and fatigue [3].

Physical activity (PA) interventions have clear beneficial effects on physical and psychosocial functioning, both during and after cancer treatment [4–7] Furthermore, a systematic review of 100 studies showed that higher levels of PA are associated with a substantially lower risk of recurrence, and of overall and cancer specific mortality [8]. Risk reductions of 20–60% have been reported in breast and prostate cancer depending on the amount and intensity of PA [9, 10]. However, survivors often do not meet the recommended PA level of ≥150 min moderate to vigorous physical activity (MVPA) per week [11]. Low levels of PA often remain low for years after treatment [12, 13]. Since cancer survivors who adhere the PA recommendation save, on average, $4686.1 (1–5 years’ survival time) in health care costs [14], efforts need to be made to encourage PA in an effective manner, in order to improve health status among survivors.

In 2015, we developed an Internet-based Physical Activity Support program (IPAS) to improve physical activity [15] and tested it in lung [16] and breast [17] cancer survivors. In breast cancer, there were some indications for the impact of the program, but the study had limited power to detect differences in subgroups (eg. during and after completion of treatment) and the study lacked a control group.

In lung cancer patients the use was limited, and effects were minimal, mainly due to the intensive treatment [16]. To date, few well-powered studies have been done using a similar distance based approach and the efficacy is limited [18].

The IPAS intervention is based on theoretical frameworks that are associated with PA motivation and behaviour in cancer survivors [19]. A meta-analysis of 85 web-based studies showed that interventions with a strong theoretical base are more likely to be effective than interventions without or with a weak theoretical base [20]. Additionally, the results of the review indicated that adding extra communication options with a counsellor, either via telephone, text message or e-mail, adds to the effectiveness of a web-based intervention. In the IPAS feasibility study, no additional communication mode was included. In focus groups conducted during the feasibility study, many participants indicated that an offline counselling moments would be helpful [21]. Therefore, we added physiotherapist counselling by phone as an extra feature, which may further enhance the outcome without large increments in costs. The aim of the present study is to investigate the (cost-)effectiveness of IPAS on short- and long-term PA levels, and to explore the added value of monthly in-person support, compared to usual care.

**Table 1 Tab1:** Concepts from TTM, TPB and specific SCT to target per stage

Stage	Targeted concepts per information set	Transtheoretical model	Theory of Planned Behaviour	Social Cognitive Theory
Stage 1 & 2	Knowledge & attitudes	Consciousness raising Dramatic relief Environmental reevaluation Self-reevaluation	Attitudes	Knowledge Outcome expectations
	Self-efficacy	Self-efficacy	Perceived behaviour control	Self-efficacy
Stage 3	Knowledge & attitudes	Consciousness raising Dramatic relief Environmental reevaluation Self-reevaluation	Attitudes	Knowledge Outcome expectations
	Self-efficacy	Self-efficacy	Perceived behaviour control	Self-efficacy
	Goals & rewards	Self-liberation Reinforcement management	–	Health goals
Stage 4 & 5	Goals & rewards	Self-liberation Reinforcement management	–	Health goals
	Social support & environment	Helpingrelationships Counterconditioning Stimulus control	Subjective norms	Social and physical environment

Legend: stage 1 = precontemplation; stage 2 = contemplation; stage 3 = preparation; stage 4 = action; stage 5 = maintainance

## Methods/Design

### Trial design

The PABLO study is a three-armed multicenter randomised controlled trial (RCT). The participants will be recruited from a specialized cancer hospital: the Netherlands Cancer Institute (NKI), Amsterdam, and a large teaching hospital: Rijnstate, Arnhem.

Participants will be randomised to one of the three study arms. Participants allocated to the first intervention arm will receive 6-month access to the intervention (IPAS). The second intervention arm will receive 6-month access to IPAS, as well as additional support by a monthly phone call with a physiotherapist (IPAS+TS). The control group will receive usual care and a leaflet with PA guidelines. The total study duration per participant is 12 months. This protocol will follow the SPIRIT guidelines. Figure 1 contains the flowchart for the study.

**Fig. 1 Fig1:**
[figure not shown]
Flowchart of the PABLO-tudy

### Aim and hypotheses

The primary aim of the study is to evaluate the effectiveness of the IPAS program (with or without additional telephone support), compared to usual care, on objectively measured PA in patients with primary breast and prostate cancer who have completed primary treatment 3–12 months ago.

We have the following secondary aims: first, to evaluate the effect of the two interventions on self-reported PA, stage of change (regarding PA behaviour), fatigue, mood and health related quality of life compared to usual care. Second, to perform a cost-effectiveness analysis to estimate the expected allocative efficiency of IPAS and IPAS+TS vs. usual care. Third, to identify potential moderators (clinical and socio-demographic characteristics) and mediators (attitudes towards PA, social support and self-efficacy) of the intervention effect on PA levels. Finally, as an exploratory aim (as the study is not powered for this comparison), to evaluate the comparative effect of IPAS alone with IPAS+TS on objectively measured PA.

We hypothesize that using IPAS or IPAS+TS will increase levels of PA more than usual care where patients only receive a leaflet with current PA guidelines. Additionally, several studies have shown the value of personal feedback to increase cancer survivors’ PA levels [20–22]. Therefore, we hypothesize that participants in the IPAS+TS group will increase their PA-levels to a greater extent than participants receiving IPAS only. Additionally, we hypothesize that increased PA resulting from the exposure to IPAS or IPAS+TS will lead to decreased levels of fatigue, and improved HRQOL and mood as compared to control. Finally, we hypothesize that total costs for IPAS will be lowest compared to IPAS+TS, due to the low intervention costs, or somewhat higher compared to UC, and “gains” for IPAS−/+TS in terms of improved QoL.

### Inclusion and exclusion criteria

#### Inclusion criteria

Patients with histologically confirmed primary breast or prostate cancer (stages: T1 – T4, N0 – N3 and M0), who may currently be receiving adjuvant endocrine treatment (breast and prostate cancer) or Trastuzumab (breast cancer) will be included in the study. Primary treatment should have been completed a minimum of 3 months and a maximum of 12 months prior to study entry. All patients need to provide written informed consent.

#### Exclusion criteria

Main exclusion criteria are a lack of basic proficiency in Dutch, serious cognitive or psychiatric problems that would preclude following the intervention or completing the study questionnaires, and lack of internet access. Patients without a digital ID (DigID), which is a Dutch digital authentication code based on one’s social security number (mostly used for governmental services) will be excluded. DigID is one of the most frequently used authentication methods in the Netherlands. Also, patients participating in concurrent studies or rehabilitation programs containing psychosocial and/or exercise interventions will be excluded, as well as patients who are unable to perform unsupervised exercise at the recommended levels or who cannot safely perform such exercise according to the pre-exercise screening recommendations of the American College of Sports Medicine [23]. Patients who have (signs of) cardiovascular, metabolic, or renal disease, can only participate after approval by the treating physician. Lastly, because our aim is to increase PA-levels of cancer survivors, we will a-priori determine, by a short interview, who already meets the PA guideline of > 150 min MVPA/week of moderate to vigorous PA for more than 6 months. To take into account a ~ 30% overestimation of self-reported PA [24], we will be excluding patients who report > 200 min/week MVPA for longer than 6 months.

### Recruitment and eligibility

In total, 246 patients will be recruited. We will include patients both retrospectively and prospectively. For the prospective part, the treating medical specialist or specialized nurse practitioners will inform the patient about the study during a follow-up appointment in the hospital. The clinician checks eligibility with the aid of a screening-list of inclusion and exclusion criteria. Interested patients will receive an information package. After two weeks, the researcher will contact the patient by phone to confirm whether or not the patient wants to participate. For the retrospective recruitment, eligible patients will be identified from medical records by the treating physician and will be sent study information by mail. If approved via a response card, the researcher will contact the patient by phone to confirm participation or non-participation.

#### Non-participation analysis

Many trials on PA behaviour change interventions show recruitment rates of around 30% [25]. We expect that, in the current trial, a substantial percentage of eligible patients will also decline the invitation to participate. To gain more insight into the characteristics of this group, the non-participants will be invited to complete a one-time online questionnaire similar to the baseline questionnaire completed by study participants. In addition, we will ask them if they are willing to report their reason(s) for not participating.

### Randomisation

Patients will be allocated to one of the three study arms, using a minimization procedure that ensures balance of the groups in terms of tumor type (breast/prostate), hospital (NKI/Rijnstate), age (> 50, 50–60, > 60), and current endocrine treatment (yes/no). Participants will be randomised by the researcher, using a computer generated random assignment procedure (ALEA, [26]) to one of the two intervention groups (IPAS or IPAS+TS) or to the usual care control group with a 1:1:1 distribution. Neither participants nor researchers will be blinded to the randomization results.

### Interventions

#### IPAS

The Internet-based Physical Activity Support intervention is structured according to the Transtheoretical model (TTM) [27] and uses aspects from the Theory of Planned behaviour [28] and Social Cognitive theory [29] (Table 1). The TTM postulates that subjects can be classified into one of five stages of behavioural change related to the desired behaviour, in this case, meeting physical activity guidelines [27]. The five stages identified are [1] precontemplation (not sufficiently active and not intending to change), [2] contemplation (not sufficiently active but willing to change within next 6 months), [3] preparation (not sufficiently active but planning to change within 1 month), action (sufficiently active but for less than 6 months) or maintenance (sufficiently active for longer than 6 months). Patients can move through the stages during the intervention. In every stage, patients receive information that matches the particular stage. This approach is essentially the same as in the pilot intervention described previously [17], but has been improved in several ways to make it more attractive by adding more and more appealing information, images, interactive assignments and video’s.

During the six months of the intervention, patients will be invited by email to fill out an online questionnaire a month after completing the previous questionnaire. Questions will be posed on current PA levels (last 7 days) and motivation to become more physically active (see Additional file 1). Based on their responses, patients will be classified into one of the TTM stages, using the behaviour of ≥150 min per week of moderate to vigorous PA as target behaviour [30]. If patients forget to complete the questionnaire, a reminder will be sent after one week. After patients have completed their questionnaire, they will be directed to a content page that provides feedback on current PA levels via a graph and a table related to cancer survivorship guidelines (i.e. ≥150 min moderate to vigorous physical activity per week and two days a week of muscle strengthening exercises) [30]. Additionally, information is provided on several topics (e.g. “benefits of exercise”, “fatigue”, “start exercising”) in writing and through videos. The videos show breast or prostate survivors (depending on the participant’s diagnosis), who explain perceived benefits from exercise, or how they have overcome barriers to exercise. Other videos show physiotherapists or a physician explaining exercise principles and benefits. Also, there are several homework assignments (e.g., setting realistic goals, seeking social support, and identifying barriers and facilitators for being (more) physically active). Although not included in the criterion for target behaviour of ≥150 min of MVPA per week, throughout the program we also encourage patients to do muscle strengthening exercises at least 2 days a week, in accordance with current guidelines for physical activity for cancer survivors [31]. Table 1 presents an overview of the approach per stage of change, and examples of content are provided in Tables 2 and 3. Additional file 2 shows an example of the advice page that will be provided to the patients. New material will be provided monthly, tailored to the patients’ current stage of change. We have developed three content sets for every stage except for the maintenance stage for which we developed two content sets. Most of the content is the same for breast and prostate cancer survivors, but texts and videos are tailored to the specific population.

**Table 2 Tab2:** Example of the provided content for the precontemplation stage

Stage 1 (precontemplation), content set 1			
Component	Targeted concept(s) (and processes of change)	Stage-appropriate strategy	Application
Information: Physical activity after cancer	Knowledge & attitudes (consciousness raising and dramatic relief)	Providing information on consequences of physical activity.	Introduction text with picture. Personal feedback on PA level of last week showed in graph and table. Written stories/quotes, Two movies (advice of a doctor and a personal testimonial of a survivor).
Assignment 1: Pros of physical activity	Knowledge & attitudes (consciousness raising)	Weighing pros and cons, emphasize pros.	Assignment on advantages of PA, including ticking options.
Assignment 2: Physical activity and significant others	Knowledge & attitudes (environmental reevaluation)	Environmental reevaluation (consequences to others).	Assignment on influence on others, including two text boxes.
Assignment 3: Past success	Self-efficacy	Prompt focus on past success (regarding exercise), with solution-focused questions.	Tips/examples, assignment on successes including text boxes.

**Table 3 Tab3:** Example of the provided content for the action stage

Stage 4 (action), content set 1			
Component	Targeted concept(s) (and processes of change)	Stage appropriate strategy	Application
Information: Physical activity after cancer	Knowledge & attitudes	Providing information on consequences of physical activity via a link, providing information on how to (start) be(ing) physically active via a link and providing information on how to stay physically active.	Introduction text with picture. Personal feedback on PA level of last week showed in graph and table. Written stories/quotes, Two movies (advice of a physiotherapist and a personal testimonial of a survivor).
Assignment 1: Keep setting goals	Goals & rewards (self-liberation, reinforcement management)	Prompt trying out new activities, keep setting a goals and graded tasks, action planning and rewarding.	Information, Tips/examples, assignment on goals stetting, including text boxes.
Assignment 2: A bad week	Self-efficacy	Relapse prevention.	Information, Tips/examples, assignment on barriers and facilitators, including text boxes.
Assignment 3: Pros of being physically active	Self-efficacy	Prompt focus on past success including gained benefits, solution-focused questions.	Testimonial of a survivor, tips/examples, assignment on successes, including text boxes.

Apart from some obvious differences, e.g. showing a female patient as a role model for breast cancer survivors and a male role model prostate cancer survivors in the videos, we tailored information texts on the benefits of exercise to the available evidence for that group. Also, information on exercising with (risk of) lymphedema is only provided to breast cancer patients.

In total, the intervention lasts for 6 months. To facilitate and stimulate use of the IPAS, the intervention is embedded in the hospitals’ patient portal. Via this portal, patients can, for example, also access their medical record and see their clinical appointments. Patients receive two positively worded reminders via email in the first two months to stimulate their participation.

#### IPAS with telephone support (IPAS+TS)

In the second intervention group, the IPAS intervention will be complemented with additional monthly support provided by a physiotherapist (IPAS+TS). With the exception of the first appointment, which will be a face to face intake, consultations will be done by phone.

During the 45-min intake, a physiotherapist will briefly introduce the study and the IPAS intervention, and discuss current PA level and motivation and barriers to PA. Subsequently, the patient will be asked to exercise on a stationary bike or treadmill, to experience the desired moderate intensity. The workload on the bike/treadmill will be determined by the physiotherapist based on heart rate and clinical signs (breathing frequency, etc.) and confirmed by ratings of perceived exertion (RPE 11–13 on a 6 to 20-point Borg scale) [32]. The intake session is concluded by making an agreement with the patient on the intended behaviour change, and by establishing the most convenient time at which the patient can be reached by telephone. Telephone calls will be scheduled as soon as patients have filled out the monthly questionnaire in IPAS, and additional calls can be made on an ad-hoc basis, when desired. Prior to the telephone call, the physiotherapist will look-up the current stage of change by reviewing the last completed online questionnaire. During the monthly call, the physiotherapist first confirms the stage of change by discussing current PA levels. Next, the physiotherapist provides feedback on the stage of change and restates the agreed behaviour from the previous (intake- or telephone-) consultation. The patient is asked to comment on her or his experiences with respect to exercise behaviour in the past period. The physiotherapist will help the patient reflect on these experiences and accompanying thoughts, and will normalize, reinforce or explain physical activity behavior whenever relevant. The telephone consultation concludes with an agreement on a behavioural goal (related to physical activity) for the next month. Physiotherapists take notes of each discussion in standardized forms (see Additional file 3).

All physiotherapists receive a two-hour-training and detailed guidelines for the intake and telephone calls. Physiotherapists are instructed to choose their words carefully so as to avoid coming across as being judgmental or directive. Also, they are instructed to support patients in finding their own solutions to experienced barriers, to normalize negative experiences and to reinforce positive experiences, whenever possible.

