### Sample size calculation

With a total sample of 195 patients (65 per group), the study will have 80% power to detect an effect size of 0.5 for the primary outcome (change in weekly time spent in MVPA) with a *p* value of 0.05. An effect size of 0.5 typically represents a group difference or change over time that is perceived as being clinically relevant [33].

In total, 246 subjects will be recruited for this study, to allow for an attrition rate of approximately 20% (i.e., subjects who discontinue participation in the study entirely, including failure to complete all follow-up measures; those who discontinue participation in one of the groups but complete the follow-up assessments will be included in the analysis). We did not chose for a forced 50–50% inclusion of breast and prostate cancer survivors. Eligible patients will be included, regardless of the tumor type. Thus, at least 195 subjects will be available for the primary intention-to-treat analysis.

**Table 4 Tab4:** Outcome measures and measurement time points

Outcome	Measured by	Baseline	6 months	12 months	Continuously
PRIMARY					
Physical Activity	Objectively (Accelerometers and GPS-trackers)	x	x	x	
SECONDARY					
Physical Activity	Self-reported (IPAQ)	x	x	x	
Stage of behaviour change	Stage of change	x	x	x	
Fatigue	MFI	x	x	x	
Mood	POMS				
Quality of life	SF-36 and EQ5D	x	x	x	
OTHER OUTCOMES					
Cost outcomes	iMCQ iPCQ		x	x	
Social-demographic and clinical data	Social-demographic questions and patient medical file	x			
Moderators and Mediators of PA	Social-demographic questions and patient medical file	x			
Non-participation data	Reasons of non-participation question + Baseline questionnaire.	x			
Compliance	Questionnaire + Portal log data		x		x
Patient evaluation of the program	Questionnaire		x		
Contamination question for control group	Question on alternative PA program participation		x	x	

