### Statistical analysis

#### Primary study parameter

Change in weekly time spent in MVPA, as measured with the accelerometer, between baseline and 6 months will be used as the main outcome parameter. We will evaluate differences over time between intervention (blended care and web-only) and usual care with a mixed-effects linear regression model adjusted for MVPA baseline scores and stratification factors.

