#### Secondary study parameter(s)

We will evaluate between-group differences over time in self-reported level of PA, fatigue, mood, and HRQOL using mixed effects linear regression models. Scores for the IPAQ, MFI, POMS, SF-36 will be calculated according to existing algorithms. Differences in mean change scores over time between the combined intervention group and the control group (blended care and web-only) will be accompanied by effect sizes. Effect sizes, defined as standardized measures of the strength of the difference in improvement between groups over time, will be calculated by subtracting the mean change scores of the control group from those of the intervention group, and subsequently dividing this by the pooled standard deviation. Effect sizes of 0.2 are considered small, 0.5 moderate, and 0.8 large [54]. The *p*-value for overall model effects will be set at 0.05, and for specific contrasts to 0.01, lowering the risk of Type I errors due to multiple testing [55]. All analyses will be conducted on an intention-to-treat basis. In addition, per-protocol analyses will be performed on patients according to compliance levels.

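### Only IPAS+TS is delivered by physiotherapists, but no therapist-level term is stated and the sample size assumes independent patients; a sensitivity analysis should cover this

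*Protocol article*

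**What the plan says.** The Protocol article, section IPAS with telephone support (IPAS+TS), states that "the IPAS intervention will be complemented with additional monthly support provided by a physiotherapist (IPAS+TS"). The physiotherapist runs a face-to-face intake of 45 minutes with a supervised exercise bout, then a monthly call that ends with an agreed behavioural goal. The same section states: "All physiotherapists receive a two-hour-training and detailed guidelines for the intake and telephone calls". So there are several physiotherapists; how many, and how patients are assigned to them, is not given. The IPAS arm is fully automated, and the control arm receives usual care and a leaflet.

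Under Primary study parameter, the analysis is a "mixed-effects linear regression model adjusted for MVPA baseline scores and stratification factors". For the other questionnaire outcomes, the section on secondary parameters reads: "We will evaluate between-group differences over time in self-reported level of PA, fatigue, mood, and HRQOL using mixed effects linear regression models". Neither section names the random effects. The Randomisation section describes a minimisation that "ensures balance of the groups in terms of tumor type (breast/prostate), hospital (NKI/Rijnstate), age" and current endocrine treatment; physiotherapist is not a factor.

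The section on sample size gives this basis: "With a total sample of 195 patients (65 per group), the study will have 80% power to detect an effect size of 0.5". The significance level there is worded "with a *p* value of 0.05". No design effect is mentioned.

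**The concern.** This is a partially nested design: patients in two arms are ungrouped, while patients in the third are grouped by the physiotherapist who counsels them. Some physiotherapists may be better than others at raising MVPA, which is the very behaviour they coach and the primary outcome. Outcomes within a caseload would then be positively correlated, and the 65 IPAS+TS patients would carry less information than 65 independent patients.

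Nothing named in the model picks this up. A hospital effect common to all three arms cannot absorb variation between physiotherapists that exists only inside IPAS+TS. If the analysis contains no further term, the interval for IPAS+TS versus usual care, which belongs to the primary aim, would be too narrow, and its test would reject a true null hypothesis more often than the nominal level.

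**Working it through.** **1. The plan's own figure.** Inputs from Sample size calculation: effect size 0.5 SD, alpha 0.05 (taken as two-sided), power 80%.
- Normal approximation: n per arm = 2 × (1.960 + 0.842)² / 0.5² = 62.8, so 63. The exact t-test needs 64.
- With 65 per arm, power is 81.3% (normal approximation) or 80.8% (exact t-test).
- Attrition: 65 / 0.8 = 81.25, so 82 per arm, and 3 × 82 = 246.

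The stated 65, 195 and 246 therefore reproduce with independent patients and no allowance for clustering.

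**2. Clustering in one arm.** The article gives neither the number of physiotherapists k nor the ICC. Both are assumed here: k = 3 to 8 and ICC = 0 to 0.05, with equal caseloads m = 65/k.
- Design effect in IPAS+TS: DE = 1 + (m − 1) × ICC.
- Ratio of the true to the independence standard error, IPAS+TS versus usual care: √[(1 + DE)/2].
- Type I error at nominal 0.05: 2 × [1 − Φ(1.960 / ratio)].
- Power at 0.5 SD with the correct standard error: Φ(0.5/SE − 1.960), where SE = √[(1 + DE)/65].

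Worked example for k = 3, ICC = 0.05: m = 21.7; DE = 1 + 20.7 × 0.05 = 2.03; ratio = √(3.03/2) = 1.23; type I error = 2 × [1 − Φ(1.59)] = 11.2%.

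| k | ICC | DE | SE ratio | Type I error | Power |
|---|---|---|---|---|---|
| any | 0 | 1.00 | 1.00 | 5.0% | 81% |
| 8 | 0.01 | 1.07 | 1.02 | 5.4% | 80% |
| 8 | 0.05 | 1.36 | 1.08 | 7.1% | 75% |
| 4 | 0.05 | 1.76 | 1.18 | 9.5% | 68% |
| 3 | 0.05 | 2.03 | 1.23 | 11.2% | 64% |

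Secondary study parameter(s) sets 0.01 for specific contrasts. At that level, the worst case in this range gives about 3.7%.

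**3. Both interventions pooled against usual care.** The ratio is √{[1 + (1 + DE)/4] / 1.5}. At ICC 0.05 it is 1.03 for k = 8, 1.06 for k = 4 and 1.08 for k = 3 (√(1.758/1.5)). Power stays at about 86% to 89%, against 91% without clustering.

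**4. Cost of putting the term into the primary model.** With few physiotherapists, the between-physiotherapist variance has very few degrees of freedom. A simulation at ICC 0 with small-sample degrees of freedom gave power of roughly 60% to 76% for 2 to 8 physiotherapists, against about 81% without the term.

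Steps 2 and 3 use the normal approximation, so the power figures there are optimistic when physiotherapists are few.

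**The case against.** A reader might infer that the stated model treats IPAS+TS patients as independent, and that standard errors for every IPAS+TS contrast are therefore too small. The text does not support that. The model is mixed-effects, its random effects are not listed (not even one for repeated measures on a patient), and the words about adjustment list covariates only. A journal article commonly leaves the random-effects structure to the full protocol or analysis plan, so silence does not show that a physiotherapist term was left out. The error also needs an ICC above zero, which the article does not establish.

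Other points weaken the case. Shared training, detailed guidelines, standardised forms and a non-directive style could all reduce differences between physiotherapists. The article does not say that one physiotherapist follows a patient from intake through all calls. IPAS+TS versus IPAS is declared exploratory and unpowered under Aim and hypotheses, so its error rate is not confirmatory. Treating a handful of physiotherapists as fixed rather than random is also defensible if no generalisation beyond them is intended.

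These arguments remove any claim that the analysis is wrong as written. Three things remain: the arm is partially nested, no term named in the article addresses that, and the power statement holds for IPAS+TS versus usual care only if the ICC is about zero. The last concerns a figure that the article fixes itself.

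**Conclusion.** The point holds conditionally and is minor. If no physiotherapist-level term is fitted and the ICC is above zero, the standard error for IPAS+TS versus usual care is understated. With 65 analysed patients per arm, 3 to 8 physiotherapists and an ICC of 0 to 0.05, the true standard error is between 0% and about 23% larger, and type I error at nominal 0.05 runs from 5% to about 11%. Over the same range, the power of a correct analysis falls from 81% to as low as 64%. The number of physiotherapists and the ICC are assumptions, and at ICC 0 there is no error at all. The pooled contrast is affected less (at most about 8% in this range). The consequence that matters is for IPAS+TS versus usual care.

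**What to change.** - Record the treating physiotherapist, or physiotherapists if more than one is involved, for each IPAS+TS patient on the standardised session forms that already exist. This is best done prospectively, since it may be hard to recover later.
- Prespecify a sensitivity analysis of IPAS+TS versus usual care with a physiotherapist random effect in the IPAS+TS arm only and small-sample degrees of freedom. If there are too few physiotherapists to estimate that variance, report the contrast over a stated range of ICC values instead.
- State in the sample size section that the 80% power assumes no clustering by physiotherapist.
- If the full protocol or analysis plan already contains such a term, say so and give the number of physiotherapists.

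The cost is one identifier and one extra analysis. With few physiotherapists, its intervals will be wide and its variance estimate imprecise. For that reason it should not replace the primary model while the number of physiotherapists is unknown.
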